## 4 BACKGROUND INFORMATION

Alzheimer's disease (AD) is the most common cause of cognitive impairment and dementia and represents over 60% of all dementia cases [Silverman et al, 2004]. The key neuropathological hallmarks of AD include the presence of extracellular deposits of beta-amyloid (A $\beta$ ) peptides, intraneuronal neurofibrillary tangles, and the predominance of neocortical neuronal degeneration [Serrano-Pozo et al, 2011]. However, despite a clinical assessment, AD is often not recognised, particularly in the early stages or if mixed pathology is present.

Alzheimer's disease is a progressive disorder and the processes underlying the disease begin years if not decades before the onset of cognitive defects or dementia symptoms. There is no fixed event to define the onset of AD or to identify the point at which an individual transitions between phases [Albert et al, 2011]. Diagnosis based on clinical criteria alone is difficult. It is estimated that around 50% of diagnoses in persons presenting with objective cognitive impairment are incorrect. Most commonly, the impairment is attributed to Alzheimer disease. The percentage of incorrect diagnoses is still substantial even in more advanced stages of the disease – comparisons to a neuropathological standard of truth reveal that up to one-third of patients are misdiagnosed [Beach et al, 2012].

Beta-amyloid (A $\beta$ ) deposition is considered to be a necessary—but not sufficient—step on the path toward development of Alzheimer's disease (AD). Depiction of brain A $\beta$  in vivo [Curtis et al, 2015][Sabri et al, 2015] can therefore improve an early diagnosis of AD, and, when recognised in a pre-symptomatic population, it might provide an opportunity for secondary prevention of dementia. Understanding the value of positron emission tomography (PET) imaging of A $\beta$  provides a unique opportunity to achieve 2 major goals: 1) improve the diagnostic workup of patients suspected to have AD [Beach et al, 2012] and their management; 2) understand the natural history of AD in a pre-symptomatic stage in order to better select patients for trials.

Through engagement with regulators, the AMYPAD consortium will maximise the value of its findings for pharmaceutical companies, healthcare providers, and patients [Frisoni et al 2017].

### 4.1.1 Utility of amyloid PET imaging in patient diagnosis and management

The value, timing, and appropriateness of amyloid PET imaging in clinical practice need to be established to allow its cost-effective implementation in the diagnosis process [Hornberger et al, 2015] of cognitive decline and dementia. This study (AMYPAD Diagnostic and Patient Management Study 01) will determine in a real-life clinical setting for whom diagnostic amyloid PET imaging is appropriate, when this is best performed, and how the resulting information is influencing diagnostic confidence, patient management, and ultimately decision trees and cost-effectiveness of dementia care.

Specifically, we will study 3 groups of patients presenting to memory clinics with a cognitive impairment due to AD, specifically those with subjective cognitive decline plus (SCD Plus), mild cognitive impairment (MCI), and dementia, to determine when amyloid PET imaging helps to exclude AD aetiology (negative predictive value) or conveys an increased risk of AD

(positive predictive value) vis-à-vis other information and evidence (clinical, structural imaging, genetic, CSF). Ultimately, the AMYPAD Diagnostic and Patient Management Study will deliver an encompassing diagnostic algorithm allowing a cost-efficient implementation of amyloid PET imaging in the clinical practice.

We will study the impact of the information provided by amyloid PET imaging beyond diagnosis by determining the impact on patient management and health resource utilisation, both in the current era of symptomatic treatment and in the context of potentially effective disease-modifying therapies aimed at lowering A $\beta$  in the brain. Furthermore, we will determine if our diagnostic algorithm is cost-effective from a health care perspective through providing the input of economic modelling, in the context of the current regulatory perspective.

#### 4.1.2 Natural history of disease

Ageing is the leading risk factor for development of AD; the prevalence of dementia is 1 in 9 people age  $\geq 65$  years, rising to 1 in 3 people age  $\geq 85$ ; and more than half of these people have AD. Genetic, environmental, and comorbid illnesses also confer risk. Indeed, the genetic risk factors in familial, early-onset AD that have provided the strongest insight into the pathophysiology of the disease as they include mutations in the amyloid precursor protein and presenilin proteins. These mutations lead to increased turnover of A $\beta$  and production of cleavage products such as A $\beta_{1-42}$ , which are prone to misfolding and formation of extracellular aggregates.

Identification of fibrillary amyloid plaques in cortex is one of the requirements for the diagnosis of AD at autopsy. While the abundance of fibrillary amyloid plaque does not correlate with degree of cognitive impairment in life, preclinical studies suggest that the soluble oligomeric of A $\beta$ , the intermediates to insoluble plaques, are neurotoxic and may trigger other neurotoxic cascades such as the spreading of phosphorylated tau, proteins that are also subject to misfolding and self-aggregation and form intracellular neurofibrillary tangles. This hypothesis is illustrated by the ‘Jack’ model of the progression of biomarkers in AD [Jack et al, 2010][Jack et al, 2013].

In the Alzheimer’s Disease Neuroimaging Initiative (ADNI) studies from US and other countries and the Australian Imaging, Biomarker & Lifestyle Flagship Study of Ageing (AIBL), all of which evaluate groups of elderly subjects with normal cognition, cognitive impairment, and dementia as a pseudolongitudinal model of disease progression, the frequency of high brain amyloid burden as measured by amyloid PET imaging rises from around 30% in healthy elders to over 80% in AD subjects. Evidence of high brain amyloid burden, either by CSF analysis or by amyloid PET imaging, has been proposed to define the earliest stages of preclinical AD [Sperling et al, 2011].

Cross-sectional and longitudinal imaging studies using amyloid PET tracers in healthy adults have shown that amyloid signal can emerge during the 6th and 7th decade of life [Vlassenko et al, 2011]. Subsequent amyloid accumulation tends to be gradual, and the rate of accumulation plateaus once a subject has reached the AD stage; although small increases may still be observed and possibly decreases in late stage disease with advanced neurodegeneration [Jack et al, 2013].

### 4.1.3 AMYPAD Diagnostic and Patient Management Study

To identify the optimal window of opportunity for possible intervention in the A $\beta$  pathway, researchers must establish in detail the sequence of events on the path towards AD.

This study will select and follow up a memory clinic population suspected of possible AD, focusing on those with subjective cognitive decline plus (SCD Plus), mild cognitive impairment (MCI), and dementia, to determine the utility of amyloid PET imaging with regards to change in diagnosis, diagnostic confidence, decision trees, and alterations between planned and actual patient management plans.

Through a European network of diagnostic memory clinics and affiliated PET centres, we will determine:

- Impact on diagnostic thinking and patient management
- Impact on diagnostic confidence and decision making
- Impact on patient reported outcomes
- Clinical utility of amyloid PET imaging in preclinical phases of AD (patients with SCD Plus)
- Costs and cost-effectiveness of early adoption vs late adoption of amyloid PET imaging
- Standardised methods of image quantitation across the PET tracers in order to perform pooled analysis across the AMYPAD program

### 4.1.4 Beta amyloid PET imaging

The development of radioligands to image A $\beta$  plaques in vivo in the human brain is an important and active area of radiopharmaceutical research. When tracers of this kind are used in combination with PET imaging, the ability to image A $\beta$  permits early and accurate differential diagnosis in cases of dementia.

Initially, the most widely used PET A $\beta$  ligand in amyloid imaging research to assess the A $\beta$  burden was  $^{11}\text{C}$  Pittsburgh compound B (PiB). The first human studies commenced in 2002 [Rowe and Villemagne, 2013]. Following publication of results from this study in 2004,  $^{11}\text{C}$ -PiB imaging spread rapidly to worldwide usage, and it led the way in A $\beta$  imaging. However, a major disadvantage of  $^{11}\text{C}$ -PiB was the 20-minute radioactive decay half-life of  $^{11}\text{C}$ , which limited its use to centres with an on-site cyclotron and  $^{11}\text{C}$  radiochemistry expertise [Villemagne et al, 2011]. It also therefore restricted its use in routine clinical research. To overcome these limitations, a number of novel tracers labelled with fluorine-18 were synthesised and tested. The half-life of fluorine-18 is 110 minutes, which allows centralised production and regional distribution of these tracers, as currently practiced worldwide in the supply of [ $^{18}\text{F}$ ]fluorodeoxyglucose for routine clinical PET imaging in oncology [Ong et al, 2013][Villemagne et al, 2011]

Two novel fluorine-18 tracer compounds, approved in the US and Europe, [ $^{18}\text{F}$ ]florbetaben (trans-4-(N-methyl-amino)-4''(2-(2-(2-[ $^{18}\text{F}$ ] fluoro-ethoxy)ethoxy)-ethoxy)stilbene) by Piramal Imaging, and [ $^{18}\text{F}$ ]flutemetamol (FLU; 2-[3-[ $^{18}\text{F}$ ]fluoro-4-(methylamino)phenyl]-1,3-benzothiazol-6-ol) by GE Healthcare Life Sciences will be utilised within this protocol

#### **4.1.5 The burden of Alzheimer's disease**

AD is the most common aetiology of dementia. The typical clinical presentation is progressive loss of memory and other areas of cognitive function together with functional impairment, ultimately leading to dependency and death.

Today, over 46 million people live with dementia worldwide. This number is estimated to increase to 131.5 million by 2050. Dementia also has a huge economic impact. The total estimated worldwide cost of dementia is \$818 billion, increasing to a trillion dollars by 2018 [\[Prince et al, 2015\]](#).

## 5 STUDY OBJECTIVES AND PURPOSE

### 5.1 Purpose of the Study

This phase 4, multicentre, open-label, randomised study will explore the impact of amyloid PET imaging on diagnostic thinking in the workup of patients with SCD-plus (subjective cognitive decline associated with features that increase the likelihood of preclinical Alzheimer's disease [AD]), mild cognitive impairment (MCI), or dementia where AD is in the differential diagnosis.

### 5.2 Research Hypothesis

The early adoption of A $\beta$  PET imaging with [ $^{18}$ F]florbetaben or [ $^{18}$ F]flutemetamol will enable an earlier etiologic diagnosis with high confidence vs the late adoption of A $\beta$  PET imaging with [ $^{18}$ F]florbetaben or [ $^{18}$ F]flutemetamol when used in patients with a cognitive impairment possibly due to AD, specifically in patients with SCD Plus, MCI, or dementia.

### 5.3 Rationale for Conducting the Study

Brain amyloidosis is one of the two key pathophysiological events of Alzheimer's disease. Amyloid PET imaging has demonstrated good analytical validity in pathologically confirmed studies, i.e. high sensitivity and specificity towards moderate or frequent amyloid plaques. However, despite effectively representing "in vivo neuropathology", its clinical utility is unclear.

AMYPAD will study in a real-life setting to what extent amyloid PET imaging affects diagnostic confidence, patient management, and ultimately the cost-effectiveness of dementia care. The dementia field has been moving from a syndromic diagnosis (e.g. "dementia") to an etiologic diagnosis (e.g. "dementia due to Alzheimer's pathology", "dementia due to Lewy body pathology", etc.). AMYPAD relies on the assumption that a more accurate etiologic diagnosis is associated with better patient care, treatment, and outcomes. The etiologic diagnosis of AD requires the detection of the two key pathophysiological phenomena of the disease, i.e. deposits of amyloid and hyper-phosphorylated tau proteins in the brain. The ascertainment of brain amyloid can rely on PET with appropriate ligands or CSF assays of A $\beta$ 42.

### 5.4 Objectives

The primary and secondary objectives of the study are as follows:

#### 5.4.1 Primary objectives

To test the hypothesis that the proportion of participants for whom the managing physician reaches an etiologic diagnosis with very high confidence ( $\geq 90\%$ ) at 12 weeks after baseline is higher for participants who underwent amyloid PET imaging shortly after baseline than for participants who have not yet undergone amyloid PET imaging (ie, participants scheduled to undergo amyloid PET imaging at 8 months [ $\pm 8$  weeks] after baseline).

## **5.4.2 Secondary objectives**

### **5.4.2.1 Diagnosis and confidence**

To assess the impact of amyloid PET imaging on other diagnosis-related metrics:

- Time to communicate to the patient an etiologic diagnosis with very high confidence ( $\geq 90\%$ )
- Changes in the managing physician's etiologic diagnosis over time.
- Changes in the managing physician's diagnostic confidence over time.
- The managing physician's estimate of the likelihood that the patient's symptoms are due to AD.
- How the placement of amyloid PET imaging in the clinical workup, when the managing physician is given free choice, changes over time.

### **5.4.2.2 Diagnostic/therapeutic management**

To assess the impact of amyloid PET imaging on patient management, including:

- Number of patients randomised to disease-modifying drug (DMD) or any other AD clinical trial at 6 months from baseline
- Change or early adoption of programs and/or pharmacologic treatments aimed to delay the onset or progression of cognitive impairment
- Use of medical resources (including but not limited to diagnostic procedures, tests, programs, visits, and hospitalisations)

### **5.4.2.3 Health economics and patient-centred outcomes**

To assess the impact of amyloid PET imaging on:

- Patient-related outcomes (cognition, anxiety, depression, coping skills, and quality of life)
- Cost of diagnostic workup to the etiologic diagnosis with very high confidence ( $\geq 90\%$ )
- Number of patients who are discharged from the memory centre and the reason for discharge

### **5.4.2.4 Imaging results assessment**

- To test the hypothesis that amyloid load is stable over 12 to 18 months.
- To develop standardised methods of image quantitation across the PET tracers in order to allow pooled analysis across the AMYPAD program.

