#### **Secondary Efficacy Analyses**

- A difference between the Early Amyloid PET arm and Late Amyloid PET arm in the time to communicate an etiologic diagnosis with a confidence  $\geq 90\%$  will be tested by the log-rank test. The cumulative incidence of diagnoses will be estimated with the Kaplan-Meier method.
- A cross-sectional difference between arms in a secondary endpoint at T1, T2, T3, or T4 will be tested with a chi-squared test if the endpoint is dichotomous, a 2-sided *t*-test if the endpoint is normal, and a Mann-Whitney test if the endpoint is categorical or continuous and non-normal. The effect of baseline characteristics such as age, gender, MMSE, etc will be studied by a linear or logistic regression model.
- A difference between study arms in the longitudinal change of a secondary endpoint will be tested by means of logistic or linear regression where the first measurement is a covariate (ANCOVA analysis) and the second measurement is the outcome. Differences in longitudinal trends between arms will also be examined by means of the mixed-effects regression model. The effects of baseline characteristics such as age, gender, MMSE, etc will be studied by including them in the regression models.
- The Free Choice arm will be divided into 3 equal-sized groups, according to the date of randomisation. For the Free Choice arm, a change in the placement of amyloid PET imaging over time in the diagnostic workup will be tested by a log-rank test.
- For participants in the Early Amyloid PET arm who had a second amyloid PET scan, the difference in amyloid load between the first and the second amyloid PET scan, as indicated by quantitative image assessments, will be tested with a paired data *t*-test. Data will be log-transformed if non-normal.
- All tests will be 2-sided, and the significance level will be set at 5%. Bonferroni corrections for multiple testing will be applied when appropriate. Point estimates will be presented, together with 95% Wald confidence intervals. A 95% nonparametric confidence interval will be constructed if the estimate is non-normal.

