**Figure 1 Study Diagram**

### 6.1.2 Follow-up amyloid PET Image visit

Participants assigned to the Early Amyloid PET arm will have an optional second amyloid PET scan (performed 12 to 18 months after the initial scan) and an additional study visit (within 28 days after the optional second scan). The change in amyloid load between scans will be quantified.

AEs that occur within 48 hours of study drug administration and all SAEs occurring within 30 days of study drug administration will be recorded.

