## 6.4 Risks and Benefits to Participants

### 6.4.1 Potential risks

This Phase 4 study uses radiopharmaceutical products whose safety and efficacy were established in Phase 1 to Phase 3 studies.

The potential risk of amyloid PET imaging is exposure to radioactivity from the tracer ( $[^{18}\text{F}]$ florbetaben or  $[^{18}\text{F}]$ flutemetamol). However, the tracer doses planned in this study are very low, and only 300 out of 900 patients will receive a maximum of 2 doses within 12 to 18 months. Dosimetry data derived from animals and humans indicate that potential radiation risks associated with studies using  $[^{18}\text{F}]$ florbetaben or  $[^{18}\text{F}]$ flutemetamol are low and comparable to those of other radio tracers [\[NeuraCeq™ SmPC\]](#)[\[Vizamyl SmPC\]](#). Specifically for this study, a maximum radiation dose of 6.1mSv/year will be administered. This ionizing radiation exposure is acceptable for the included subjects. The reasoning behind this is that, according to ICRP guidelines, the relative detriment for adults over 50 years of age is one fifth or one tenth of the 6.1mSv, the latter being based on radiation exposure of the whole population. As such, the relative dose for detriment assessment (corrected to adult dose) for a subject is between 0.61 and 1.22mSv, which is category IIa to IIb risk level for the volunteer. According to ICRP guidelines this is justified if the level of societal benefit is intermediate to moderate, which is the case of this study.

The recommended activity for an adult is 300 MBq ( $\pm 20\%$ ) for  $[^{18}\text{F}]$ florbetaben [\[NeuraCeq™ SmPC\]](#) and 185 MBq ( $+10\%$ ) for  $[^{18}\text{F}]$ flutemetamol [\[Vizamyl SmPC\]](#).

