## **12.6 Secondary Analyses**

### **12.6.1 Secondary efficacy variables**

In the analyses of the secondary efficacy variables, a cross-sectional difference between arms in a secondary endpoint at T1, T2, T3, or T4 (see Table 1) will be carried out by a chi-squared test if the endpoint is dichotomous, a 2-sided *t*-test if the endpoint is normal, and Mann-Whitney test if the endpoint is categorical or continuous and non-normal. The effect of baseline characteristics such as age, gender, MMSE, etc will be studied by a linear or logistic regression model.

A difference between study arms in the longitudinal change of a secondary endpoint will be tested by means of logistic or linear regression where the first measurement is a covariate (ANCOVA analysis) and the second measurement is the outcome. Differences in longitudinal

trends between arms will also be examined by means of the mixed-effects regression model. The effects of baseline characteristics such as age, gender, MMSE, etc. will be studied by including them in the regression models.

All tests will be 2-sided and the significance level will be set at 5%. Bonferroni corrections for multiple testing will be applied when appropriate. Point estimates will be presented together with 95% Wald confidence intervals. A 95% non-parametric confidence interval will be constructed if the estimate is non-normal.

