#### 12.6.1.4 Quantitative Imaging Results Assessment

PET images will be analysed centrally for quantitative imaging endpoints, as follows:

- Descriptive analysis of local visual assessment results
- The distributions and mean standardised uptake value ratio (SUVR) of the composite cortical brain regions, and converted to the centiloid scale, across amyloid PET tracers and by diagnostic subgroup.
- The distributions and mean SUVR of defined brain regions across amyloid PET tracers and by diagnostic subgroup.
- For each of the amyloid PET tracers, the composite cortical quantitative uptake (SUVR and SUVR converted to the centiloid scale) versus the local site visual reading interpretation and classification confidence.

For participants in the Early Amyloid PET Imaging arm who have a second amyloid PET scan:

- The distributions and mean change in standardised uptake value ratio (SUVR) of the composite cortical brain regions, and converted to the centiloid scale, across amyloid PET tracers and by diagnostic subgroup.
- The distributions and mean change in SUVR of defined brain regions across amyloid PET tracers and by diagnostic subgroup.
- The difference in amyloid load between the first and the second amyloid PET scan, as indicated by quantitative image assessments, will be tested with a paired data *t*-test. Data will be log-transformed if non-normal.

A SCD-specific sub-study aiming at investigating the impact of PET-amyloid result disclosure will be performed on the SCD participants. This specific protocol is submitted separately as an AMYPAD DPMS sub-study.

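### The objective is to test that amyloid load is stable, but the only planned test, a paired t-test of zero mean change with no margin, can reject stability and never support it

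*Protocol*

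**What the plan says.** The objective is worded as a hypothesis of stability, identically in the Synopsis and in section 5.4.2.4: "To test the hypothesis that amyloid load is stable over 12 to 18 months".

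The analysis is in section 12.6.1.4. The difference in load between the two scans, "as indicated by quantitative image assessments, will be tested with a paired data" t-test, with log-transformation if the data are non-normal. The Synopsis (Secondary Efficacy Analyses) names the same test for the same people, in a sentence that opens "For participants in the Early Amyloid PET arm who had a second amyloid PET scan, the difference in amyloid load between the first and the" and goes on to the later scan. Section 12.6.1 sets the error rate for all secondary tests: "All tests will be 2-sided and the significance level will be set at 5" per cent.

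The number of pairs is left open. Section 6.1.2 says "Participants assigned to the Early Amyloid PET arm will have an optional second amyloid PET scan", and section 13.4.2 requires a further consent for it. The only figure that bounds the number is in section 6.4.1: "only 300 out of 900 patients will receive a maximum of 2 doses within 12 to 18 months". Expected uptake is not stated, and the sample size calculation in section 12.7 deals only with the 12-week diagnostic-confidence endpoint.

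Estimation is also planned. Section 12.6.1 says "Point estimates will be presented together with 95% Wald confidence intervals". Sections 10.1.2.4 and 12.6.1.4 list the distribution and mean of the change in SUVR and centiloid, and the Synopsis lists shifts between amyloid-positive and amyloid-negative reads. None of these comes with a criterion for calling load stable.

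**The concern.** A difference test puts the hypothesis of interest in the null. A significant result counts against stability. A non-significant result leaves the question open, because it may mean no change or too few pairs to see one. The objective sets out a hypothesis of stability, yet no outcome of the planned test would count in its favour.

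The behaviour with sample size is also the wrong way round. With few pairs, a real change tends to go undetected. With many pairs, a change too small to matter can reject the hypothesis. Section 4.1.2 makes a small non-zero change plausible for part of the sample ("Subsequent amyloid accumulation tends to be gradual"), and that is where the test says least. At stake is the conclusion the study may draw on whether load is stable between repeat scans: it could turn on uptake of an optional scan rather than on the size of the change.

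**Working it through.** **No figure to reproduce.** The protocol gives no margin, SD of change, expected number of pairs or power for this objective. The effect sizes, margins and pair counts below are therefore illustrations, expressed in units of the SD of the within-person change.

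**Inputs from the protocol:** paired t-test (12.6.1.4 and Synopsis); two-sided 5% (12.6.1); at most 300 pairs (6.4.1).

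**Assumed:** true mean change d = 0.2 or 0.3 SD; 30, 100, 270 or 300 pairs. The 270 is 300 less 10%. That 10% is the withdrawal allowance for the 12-week endpoint in section 12.7, not an estimate of second-scan uptake.

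**Step 1: chance that the planned test rejects stability.** With n pairs, ν = n − 1, t* the 97.5% point of t on ν degrees of freedom, and non-centrality δ = d√n:

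power = 1 − F(t*; ν, δ) + F(−t*; ν, δ), where F is the noncentral t distribution function.

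For n = 100 and d = 0.2, δ = 0.2 × 10 = 2.0 and power = 0.508.

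**Step 2: half-width of the 95% interval**, t*/√n in SD units. For n = 100 it is 0.198.

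| Pairs | Rejects, d = 0.2 | Rejects, d = 0.3 | 95% CI half-width (SD) |
|---|---|---|---|
| 30 | 0.185 | 0.355 | 0.373 |
| 100 | 0.508 | 0.844 | 0.198 |
| 270 | 0.906 | 0.998 | 0.120 |
| 300 | 0.932 | 0.999 | 0.114 |

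**Step 3: what a non-significant result is worth.** If the true change is exactly zero, the test is non-significant 95% of the time at any n. At 30 pairs and d = 0.2 it is non-significant 1 − 0.185 = 81.5% of the time, so the result hardly separates the two cases. At 270 pairs the same change gives 1 − 0.906 = 9.4%. The true change is the same; only the number of pairs differs.

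**Step 4: what a test of stability would need.** Conclude stability only if the 90% interval for the mean change lies within ±m, which is two one-sided 5% tests. With true change zero, the approximate number of pairs for 80% power is ((1.645 + 1.282)/m)²; for 90% power, 1.282 is replaced by 1.645.

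| Margin m (SD) | Pairs for 80% | Pairs for 90% | Power at 30 / 100 / 270 pairs |
|---|---|---|---|
| 0.2 | 215 | 271 | 0.000 / 0.269 / 0.899 |
| 0.3 | 96 | 121 | 0.054 / 0.820 / 0.999 |
| 0.5 | 35 | 44 | 0.698 / 0.999 / 1.000 |

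The powers in the last column are simulated. Here more pairs make a correct claim of stability more likely, which is how a test of this objective should behave.

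**The case against.** The strongest reply is that the objective says test, not show. A t-test of zero change does test stability in the sense that it can refute it, and the planned intervals and change summaries tell the reader how large a change remains compatible with the data. That is fair. It would be too strong to say that the hypothesis cannot be addressed at all, or that a bare p-value decides the matter. What remains is that an interval cannot decide for stability without a margin fixed beforehand, and the protocol fixes none.

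A reader might infer several stronger points that the protocol does not support:

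- **That stability will be claimed from a non-significant result.** Nothing says so. It is only the one way in which this test could be made to favour the objective.
- **That the subset is small.** The second scan is optional, but the only stated bound is 300. The mismatch does not depend on size.
- **That the change must be annualised.** The objective concerns a 12-to-18-month window, not a yearly rate. Annualising changes the estimand and assumes linear change.
- **That the background predicts change throughout.** Section 4.1.2 also says that accumulation levels off by the AD stage, so near-stability is plausible in part of the sample.

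Section 6.1.1 defines amyloid load by visual reads, with quantitative load reserved for disease modelling, so the planned visual shifts also bear on stability. They carry no stability criterion either, and the two-scan comparison in section 12.6.1.4 is explicitly quantitative. Finally, the separate SAP, which is not shown, may add a margin. The protocol nevertheless already fixes both the hypothesis and a test that does not match it, so this is more than detail left open.

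**Conclusion.** The point holds as a mismatch between a stated hypothesis and the test fixed for it. The planned analysis can reject stability but cannot support it, and no margin is given that would let the planned intervals do so. Under an assumed true change of 0.2 SD, the chance of rejecting runs from 19% at 30 pairs through 51% at 100 to 91% at 270, so uptake of the optional scan largely drives the result. Those figures rest on assumed effect sizes and pair counts; the mismatch itself does not.

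The consequence is limited. This is one secondary objective, in one arm, and it does not touch the primary endpoint, the randomisation or the sample size.

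**What to change.** Take one of two routes.

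1. **Keep the stability objective.** In section 12.6.1.4 and the Synopsis, conclude that load is stable only if the 90% confidence interval for the mean centiloid change over the 12-to-18-month window lies inside a margin that the sponsor fixes before analysis (two one-sided 5% tests).
2. **Drop the stability claim.** Reword the objective in section 5.4.2.4 and the Synopsis to *estimate the change in amyloid load with its 95% confidence interval*, and state that a non-significant t-test will not be read as stability.

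Scaling the change to the actual scan interval can be added as a sensitivity analysis; it is optional.

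Neither route needs new visits or data. The first requires agreement on one margin and makes stability harder to claim with few pairs: for a margin of 0.3 SD, power is about 5% at 30 pairs and 82% at 100 when the true change is zero. The second costs only wording, since the estimates and intervals are already planned.
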